### **2.2 Secondary Aims**

1. Demonstrate rural home hospital care improves days at home, physical activity, and readmission.

- For example: reduced length of stay, increased daily steps and hours of physical activity per day.

2. Synthesize lessons learned to prepare a dissemination guide for a future multi-site implementation.

- For example: clinical and administrative data including data collected from the process measures and qualitative interviews with patients and caregivers.
- Clinician process measures survey with rural home hospital clinicians
- Qualitative interviews with rural home hospital clinicians.

Please refer to our performance measures below for more details regarding the definitions and sources for each of these measures

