**Figure 2**

#### 4.3 Treatment Assignment

- If the participant consents, the research assistant will proceed to randomization via concealed envelopes with
  - Concealed allocation;
  - Stratified on diagnosis:
    - infection,
    - heart failure,
    - chronic obstructive pulmonary disease or asthma, and
    - other diagnosis;
  - Randomly selected block sizes between 4 and 6;
  - Use randomization to determine arm.
- If patient/caregiver does not consent, the research assistant will ask the patient's permission to collect covariates, functional status, and a quality-of-life measure to determine generalizability of enrollment.
- Participants randomized to the control group will receive usual care at the hospital, from an attending general internist.

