## 5.0 STUDY PROCEDURES

### 5.1 Study visits and measured parameters

Standard admission group:

An activity tracker (Vitalpatch-discussed under section 5.3) will be placed on all subjects in the control group during admission only. Subjects in the control group will receive usual care at the hospital, from an attending general internist.

Rural home hospitalization group (intervention group):

Each day, the RHH clinical team will make in-person and/or virtual visits to the patient's home. These are personnel who have been trained in home health and carry out home health as per the usual care they deliver. They have received additional training in RHH. The RHH module offers most of the same medical components that are standard of care in an acute care hospital (**Table below**). The typical staff (MD, RN, or paramedic), diagnostics (blood tests, vital signs, telemetry), intravenous therapy, and oxygen/nebulizer therapies will all be available.

RHH improves upon the components of a typical ward's standard of care in several ways:

- Minimally invasive continuous vital signs, telemetry, and activity tracking
- 24/7 clinician video visits;
- Ambulatory/portable infusion pumps that can be worn on the hip;

| Component     | Module                                                                                                                                                                                                                                                                                                                                                                                                                                                                                                                 |
|---------------|------------------------------------------------------------------------------------------------------------------------------------------------------------------------------------------------------------------------------------------------------------------------------------------------------------------------------------------------------------------------------------------------------------------------------------------------------------------------------------------------------------------------|

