## 5.3 Devices to be used

- Home hospital employs standard devices during the usual care of hospitalized patients. For example, a nebulizer machine.
- Telehealth platform: Biofourmis AI platform, biovitals® Hospital@Home. Biofourmis has completed their cybersecurity assessment and has been vetted by the Partners data sharing committee. The Biofourmis tablet serves as the communication hub and facilitates videoconferencing between the patient and physician/RN/EMT-P and it captures biometric data.
- Home hospital additionally employs
  - Vital signs monitoring patch: Vital Connect VitalPatch (FDA cleared application/use)
    - The patch will be placed on subjects in both groups, it includes a built-in activity tracker (we will use the activity tracker for control group subjects during hospital admission)
  - Ambulatory infusion pump: Smiths Medical CADD Solis VIP (FDA cleared application/use)
  - Point of care diagnostic meter: Abbott iSTAT (FDA cleared application/use) or Siemens EPOC (FDA cleared application/use)
  - Digital stethoscope (Eko; FDA cleared application/use)
  - Point of care ultrasound (Philips Lumify; FDA cleared application/use)

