### Quality: High-Value Care

| Measure                            | Source                                                       | Day(s) Obtained |
|------------------------------------|--------------------------------------------------------------|-----------------|
| Pain management                    | RA via MD/RN for home patients; RA EHR review for inpatients | Daily           |
| Hours of sleep per day             | RA via activity tracker                                      | Daily           |
| Hours of sleep per night           | RA via activity tracker                                      | Daily           |
| Hours of activity per day          | RA via activity tracker                                      | Daily           |
| Hours of activity per night        | RA via activity tracker                                      | Daily           |
| Hours of sitting upright per day   | RA via activity tracker                                      | Daily           |
| Hours of sitting upright per night | RA via activity tracker                                      | Daily           |
| Daily steps                        | RA via activity tracker                                      | Daily           |

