We *a priori* plan to perform a subgroup analysis that does not involve any extreme outlier participants (upper quartile plus 3 times the interquartile range) in either study arm, should this occur. We also *a priori* plan subgroup analyses by diagnosis, by age group, and by daily activity level. We may choose to employ non-parametric tests of significance should our data be nonparametric. We *a priori* plan to perform a subgroup analysis between continuous monitoring and intermittent monitoring sites. We *a priori* plan to perform a subgroup analysis by admission source (“from ED” vs “from ward” vs “from home”). We also plan to perform a secondary a priori subgroup analysis of US vs Canada.

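### The planned subgroup by daily activity level is undefined, and the only measures that fit it are recorded after randomisation and are expected to respond to treatment

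*Protocol*

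**What the plan says.** Protocol section 6.1 (Quantitative) commits in advance to subgroup analyses "by diagnosis, by age group, and by daily activity level". It gives no measure, time point or cut-point for activity, and it does not name the outcome to be compared within these subgroups.

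The rest of the protocol shows which activity data will exist:

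- **Allocation.** Section 4.3: "If the participant consents, the research assistant will proceed to randomization via concealed envelopes".
- **Device.** Section 5.3: "The patch will be placed on subjects in both groups, it includes a built-in activity tracker". Section 5.1 adds that for controls it "will be placed on all subjects in the control group during admission only".
- **Measures.** The High-Value Care table in section 5.5.3 lists "Hours of activity per day" and daily steps as exploratory endpoints, taken from the tracker each day. The same table has hours sitting upright, and section 5.5.2 has the share of the day spent lying down.
- **Intended effect.** Secondary Aim 1 in section 2.2 is to "Demonstrate rural home hospital care improves days at home, physical activity, and readmission", with the example "increased daily steps and hours of physical activity per day". The power analysis in section 6.1 expects 65% fewer hours lying down in the home arm.
- **Baseline.** The covariate table has no activity measure. The nearest admission items are the activities of daily living and instrumental activities of daily living questionnaires, listed under functional status.

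**The concern.** A subgroup analysis keeps the protection of randomisation when the grouping variable is fixed before allocation or cannot be changed by it. Diagnosis and age meet that condition. Activity measured during the admission does not, because the trial sets out to change it.

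Suppose sicker patients move less and cost more, and home care raises activity. Some home patients then reach the high-activity group who would have fallen in the low group as controls. In either group, home patients are on average sicker than the controls they are compared with. A within-group cost ratio then mixes the treatment effect with a severity difference that the grouping itself created. The a priori label would lend such results more credibility than they deserve.

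**Working it through.** The protocol states no figure on this point, so there is nothing to reproduce. The check has two parts.

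**1. Timing and intent.** Consent leads straight to randomisation (4.3). The tracker is worn during the admission by patients already in an arm (5.1, 5.3). Its readings are listed as endpoints (5.5.2, 5.5.3), and treatment is meant to improve them (2.2). A subgroup built from these data therefore conditions on a variable measured after allocation and expected to respond to it.

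**2. Illustrative size.** The following inputs are assumptions, not figures from the documents.

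- Severity U is standard normal, and mean cost is proportional to exp(gU) in both arms, so the true cost ratio is 1.00.
- Activity is A = dT - rU + noise, with unit variance within each arm. T is 1 for home and 0 for control.
- d is 0.3 to 1.0 SD, r is 0.3 to 0.5 (activity-severity correlation -r) and g is 0.5.
- Both arms are split at the pooled median, which is d/2.

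Weighting by exp(gU) shifts the mean of A by -rg. With Φ the standard normal distribution function, the home-to-control ratios of mean cost are:

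- High activity: [Φ(d/2 - rg)/Φ(d/2)] ÷ [Φ(-d/2 - rg)/Φ(-d/2)]
- Low activity: [Φ(-d/2 + rg)/Φ(-d/2)] ÷ [Φ(d/2 + rg)/Φ(d/2)]

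For d = 1.0 and r = 0.5, rg = 0.25:

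- High: (0.5987/0.6915) ÷ (0.2266/0.3085) = 0.866/0.735 = 1.18
- Low: (0.4013/0.3085) ÷ (0.7734/0.6915) = 1.301/1.118 = 1.16

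| d (SD) | r | Low half | High half |
|---|---|---|---|
| 0.3 | 0.3 | 1.03 | 1.03 |
| 0.5 | 0.5 | 1.08 | 1.09 |
| 1.0 | 0.5 | 1.16 | 1.18 |
| 0 | any | 1.00 | 1.00 |
| any | 0 | 1.00 | 1.00 |

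Simulation with 2,000,000 patients per scenario agrees with these values, and the overall ratio stays at 1.00 throughout. In the 1.0 SD case, 69% of home patients but 31% of controls fall in the high half. With the weaker slope g = 0.3, the range is about 1.02 to 1.10.

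**Sensitivity to the cut.** If each arm is split at its own median, all ratios return to 1.00 in this model, because the assumed activity shift is the same for every patient.

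**Precision.** With 66 per arm halved to about 33 and the protocol's dispersion of 1.2, the standard error of a subgroup log ratio is √(1.2 × 2/33) = 0.27. The 95% interval multiplies or divides the estimate by about exp(1.96 × 0.27) = 1.7.

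**The case against.** The strongest reply is that the protocol never says the tracker will be used. The factor stands beside two baseline variables, admission function is collected, and a statistical analysis plan that is not at hand could define it. If an admission questionnaire was meant and answered before allocation, the problem disappears. This stands as a limit on certainty. It does not remove the point, because the wording matches the tracker measures, while the protocol files the questionnaires under another name, functional status.

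A reader might also infer a cost bias of 3 to 18%, as large as the 10% reduction in the primary aim. The documents do not support that. The shift, correlation and slope are assumed, the pooled median is assumed, and within-arm medians give no bias in the same model. Section 6.1 does not even name cost as the outcome of these subgroups, although it is the natural reading. A shift of 3 to 18% is also small beside a 95% interval that spans a factor of 1.7 either way.

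A reader might further infer false effect modification or a false claim of savings. Under the median split, the two halves are shifted almost equally (1.16 and 1.18 at most), so little spurious difference between subgroups appears. In these scenarios the shift runs against home care. What remains is that neither half estimates the treatment effect for an identifiable kind of patient.

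**Conclusion.** The point holds in conditional form. Section 6.1 pre-plans a subgroup on an undefined activity level, and the only matching data are recorded after randomisation and are expected to respond to treatment. Splitting both arms at a common cut on those data breaks the randomised comparison within each subgroup if activity and the outcome share causes such as severity. That treatment changes activity is the protocol's own aim. That severity drives both activity and cost is plausible but not documented.

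The range of about 1.03 to 1.18 for a true ratio of 1.00 is an illustration under stated assumptions, not an estimate for this trial. The primary comparison is untouched, and the protocol attaches no power or decision to this subgroup. The correction is worth making because it is nearly free.

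**What to change.** In section 6.1, replace the activity factor in the subgroup list with a functional measure already collected at admission, for example activities of daily living. State that the value must describe the patient's state before randomisation and be recorded before allocation. Both conditions need to be written in: section 5.5 places the patient survey at admission without saying whether it precedes randomisation, and answers given once the arm is known could be coloured by it. Fix the cut-point in advance. Analyse tracker activity and posture only as outcomes.

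The cost is one phrase in 6.1 and a line on survey timing, with no new data items and no change in sample size. The downside is that the subgroup question becomes whether the effect differs by baseline function, not by activity during the admission.

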### ***Power analysis***

A priori (based on data from our previous randomized controlled trial of urban home hospital care), we expect the mean cost to be mean cost on intervention to be 40% lower than in control (leading to a ratio of mean costs in treatment to control to be at most .6). Thus, for our power calculation, we want to be able to detect that the exponential of the treatment effect in our

gamma regression to be 0.6 or lower., We will require 132 patients total (66 in each arm, and 44 total per site) to detect a 40% relative decrease in mean direct cost in home versus hospital (power: 80%, alpha: 0.05, two-tailed) using the Wald test for the treatment effect from a gamma regression model for costs discussed above. In this power calculation, we assume the over-dispersion parameter for the gamma distribution variance is 1.2 (as seen from our preliminary data). Although we hope to recruit 75 patients in each arm, 66 patients will give us more than adequate power (80%) to detect the clinically expected difference.

Secondary outcomes require slightly larger samples sizes at 80% power (with Type 1 error of 1%, approximately the type 1 error when using the Benjamini-Hochberg method as noted above). For Cost, discharge to 30-days, using a gamma regression model similar to total costs, with 66 patients in each arm, we have 80% to see an expected 65% reduction in the mean for intervention to control (we assume the over-dispersion parameter for the gamma distribution variance is 2.8 as seen from our preliminary data). For number of hours per day laying down (equivalently, % of day Lying down), using a negative binomial regression model with a logistic link with treatment and site effects, with 66 patients in each arm, we have over 90% to see an expected 65% reduction in the number of hours lying down for intervention to control (we assume the over-dispersion parameter for the negative binomial distribution is 1.4 as seen from our preliminary data). For percent with 30-day readmission, using logistic regression model with treatment and site effects, with 66 patients in each arm, we have 80% to detect on odds ratio of 0.25 for intervention on control (assuming the percent 30 day readmission in controls is 23% as seen in preliminary data). For the number of days at home, using a log-normal distribution with treatment and site effects, with 66 patients in each arm, we have over 80% to see an expected 65% increase in the number days at home for control to intervention (from 29 days to 48, days assuming the over-dispersion parameter for the negative binomial distribution is 1.4).

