## **2.0 SPECIFIC AIMS**

### **2.1 Primary Aim**

Accomplish at least a 10% reduction in hospitalization cost for select hospitalized adults who would normally have been admitted to the hospital in a rural area.

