#### **Patients:**

- Acutely ill patient is screened and recruited as above (section 3.3).
- 50 patients at each study site
- If the patient meets eligibility and agrees to enroll in the study the research assistant will contact the on-call rural home hospital MD or Advanced Practice Provider (APP) who will assess the patient’s clinical criteria by EHR review.

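### On the protocol's own inputs, 66 patients per arm give about 76% power, not 80%; 80% needs 146 patients in total, and the planned 150 give about 81%

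*Protocol*

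**What the plan says.** The Power analysis under protocol section 6.1 gives the size in these words: "We will require 132 patients total (66 in each arm, and 44 total per site". The effect that this number is meant to find is a mean cost 40% lower at home than in hospital. The error rates are set at 5% two-sided with 80% power, and the calculation is made "using the Wald test for the treatment effect from a gamma regression model for costs". On the variance the section says: "we assume the over-dispersion parameter for the gamma distribution variance is 1.2". It presents 75 per arm as something hoped for, and concludes that "66 patients will give us more than adequate power (80%) to detect the clinically expected difference".

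Section 6.1 fixes the model as a gamma regression with log link, with arm and site as fixed effects. Section 3.3 names three sites. Section 4.1 sets recruitment at "50 patients at each study site", without qualification.

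Section 2.1 words the primary aim as: "Accomplish at least a 10% reduction in hospitalization cost".

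**The concern.** Every input to the sample size is stated, so the figure can be checked without any assumption from outside the document. It does not reproduce. The document labels 132 as the required number and 75 per arm as a hope, so a team short of time or money could stop at 132 believing that 80% power was secured. The remark that 66 per arm is better than adequate would support that decision. The power statements for the secondary outcomes also take 66 per arm as their base.

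The second, smaller matter is that the aim carries a 10% threshold. The test described is against no difference, and the sizing is for 40%. A reader of the results could not tell from the protocol which of the three defines success.

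**Working it through.** **Inputs, all from section 6.1 and its Power analysis**
- Ratio of mean costs 0.6, so |ln 0.6| = 0.5108.
- Gamma dispersion φ = 1.2 (variance = φ × mean²).
- Two-sided alpha 0.05 (z = 1.960); target power 80% (z = 0.842).
- Log-link gamma model, Wald test of the arm coefficient, equal arms.

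**Formula.** With a log link and gamma variance, the variance of the estimated log ratio is φ(1/n₁ + 1/n₂) when the arms are balanced within sites. So SE = √(2φ/n), with n per arm.

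**Trying to reproduce the stated 80% at 66 per arm**
- Solving for the dispersion: φ = 66 × 0.5108² / (2 × (1.960 + 0.842)²) ≈ 1.097. The stated value is 1.2.
- √1.2 = 1.095, used as the dispersion, returns exactly 66 per arm and 80.1%. A square root taken by mistake would explain the figure, but that is an inference, and it is not a valid reading of the stated parameter. The same slip is not evident in the 30-day cost calculation: there φ = 2.8, alpha 0.01 and ratio 0.35 give 84.8% at 66 per arm.
- Other readings at 66 per arm also miss: a one-sided test gives 84.9% (57 per arm needed); 1.2 read as the gamma shape (φ = 1/1.2) gives 89.5% (51 per arm); 1.2 read as a coefficient of variation (φ = 1.44) gives 68.6% (87 per arm). If 1.2 were rounded up from 1.15, power would be 78.1% (70 per arm).

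**With the inputs as stated**
- Power at 66 per arm: SE = √(2.4/66) = 0.1907; 0.5108/0.1907 = 2.679; Φ(2.679 − 1.960) = 76.4%.
- Size for 80%: n = 2 × 1.2 × (1.960 + 0.842)² / 0.5108² = 72.2, so 73 per arm and 146 in total. The stated size is 146 − 132 = 14 short.
- Power at 75 per arm: SE = √(2.4/75) = 0.1789; 0.5108/0.1789 = 2.856; Φ(2.856 − 1.960) = 81.5%.

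**Cross-checks.** A noncentral t gives 75.8% at 66 per arm and 81.0% at 75. In 20,000 simulated three-site trials with a site-adjusted fit, the rejection rate depends on how the dispersion is handled:

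| Dispersion | 66 per arm | 75 per arm |
|---|---|---|
| Known | 76.2% | 81.1% |
| Maximum likelihood | 76.7% | 81.8% |
| Pearson | 76.9% | 82.0% |
| Deviance-based | 70.2% | 76.3% |

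No version reaches 80% at 66 per arm. The deviance-based test is conservative: with no true difference it rejects in about 4% of trials.

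**The 10% threshold, if the dispersion is 1.2**
- Smallest observed reduction that is significant: 1 − exp(−1.960 × 0.1907) = 31% at 66 per arm; 1 − exp(−1.960 × 0.1789) = 30% at 75 per arm.
- If the true ratio is 0.60, the chance that the upper 95% limit falls below 0.90 is Φ(ln(0.90/0.60)/SE − 1.960), with ln 1.5 = 0.4055. At 66 per arm this is Φ(2.126 − 1.960) = 57%; at 75 per arm, Φ(2.267 − 1.960) = 62%.

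**The case against.** The strongest reply is that the trial is not planned at 132. Section 4.1 sets 50 per site, there are three sites, and 150 patients give about 81% on the protocol's own inputs. No rule says that recruitment stops at 132. Even at 66 per arm, the ratio detectable with 80% power is 0.586, a 41% reduction in place of 40%. All of this stands, and it limits the consequence. A reader might infer that the trial as planned is underpowered; section 4.1 does not support that. What remains is that the sentence on required size is wrong, and that the text ranks the sufficient number below the insufficient one. The margin is also thin: 150 is only 4 patients above 146.

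A second tempting inference is that the trial cannot answer its primary aim, since power for a true reduction of exactly 10% is only about 9% (8.6% at 66 per arm, 9.1% at 75). The documents do not support this as an error of calculation. The Power analysis openly plans for an expected 40% reduction, taken from the earlier urban trial, and claims no power for 10%. Planning for the expected effect is a common choice, and a true reduction of 40% satisfies an aim of at least 10%. Nor is the aim out of reach: if the truth is 40%, there is a 57% to 62% chance that the confidence interval excludes reductions smaller than 10%. What stands is narrower: the aim names a threshold that the described test does not address. How the threshold is to be judged may be set out in an analysis plan that is not at hand.

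**Conclusion.** The stated size and power are wrong as written. With dispersion 1.2, ratio 0.6 and a two-sided 5% Wald test, 132 patients give about 76% power and 146 are needed for 80%. The error is 3.6 percentage points of power, or 14 patients. It takes effect only if recruitment ends at or near 132.

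These figures assume equal arms, balance of arms within sites, the dispersion exactly as stated, and a dispersion estimate that is not the deviance-based one. The preliminary data behind the 1.2 are not in the document, and a different value in the trial would move every figure here.

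The mismatch between the 10% aim and a test against no difference is a lesser point of consistency. Its practical meaning is that, with dispersion 1.2 and 150 patients, an observed reduction of between 10% and just under 30% would meet the number in the aim and yet not be statistically significant.

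**What to change.** In the Power analysis, replace the sentences on required size with: *With a gamma dispersion of 1.2 and a ratio of mean costs of 0.6, 146 patients (73 per arm) give 80% power at two-sided alpha 0.05; 132 give 76%; the planned 150 (50 per site, 75 per arm) give about 81%.* Name 150 as the recruitment target, and remove the statement that 66 per arm is enough. If the dispersion actually used was not 1.2, state the value used and where it comes from.

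In section 2.1, align the aim with the test: a difference in mean hospitalization cost between arms, with the trial powered for a 40% reduction. If the 10% threshold is to stay, state how it will be judged. One option is to require the upper 95% limit of the ratio to lie below 0.90, quoting the 57% to 62% probability above.

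The cost is restated figures and wording. No patients are added beyond the 150 already planned.

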#### 5.5.2 Secondary endpoints

| Measure                                                                                                       | Source                     | Day(s) Obtained         |
|---------------------------------------------------------------------------------------------------------------|----------------------------|-------------------------|
| Total cost, discharge to 30-days post discharge (published as percent change given sensitivity of these data) | Hospital accounting system | 30 days after discharge |
| Unplanned readmission within 30-days of discharge, %                                                          | EHR and patient report     | 30 days after discharge |
| Days at home (the number of days spent at home from the day of discharge to 30-days later)                    | EHR and patient report     | 30 days after discharge |
| Percent of day lying down                                                                                     | Biometric monitor          | Each day of             |

|  |  |           |
|--|--|-----------|
|  |  | admission |
|--|--|-----------|

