## **6.0 BIOSTATISTICAL ANALYSIS**

### **6.1 Quantitative**

We will present descriptive data with counts and percentages, means and 95% CIs, or medians and interquartile ranges, as appropriate.

The primary outcome (hospitalization cost) will be analyzed between arms, adjusted for site as a fixed effect, which accounts for difference across the three sites. . However, we will present cost data as the percentage of change in mean costs from control (rather than absolute difference) because of the sensitive nature of these data. The primary outcome will be assessed using a generalized linear model assuming a gamma distribution with a log link, given the skewed nature of cost, with treatment arm (control arm as the reference group) and site as fixed effects. The exponential of the treatment effect in this gamma regression model exactly equals the effect of interest (the percentage change from control). Patient characteristics should balance out across the two arms due to randomization, but if not, in the gamma regression, we will adjust for any of the follow patient characteristics that differ across arms: sex, age (continuous), education, and comorbid condition count (continuous). We *a priori* plan to also adjust for COVID case burden at each hospital only if COVID impacted home hospital operations. If the degree of rurality was different between patients at different sites, we *a priori* plan to adjust for degree of rurality.

We will use this same multivariable regression approach for secondary outcomes, using logistic regression for binary outcomes (e.g., readmissions) and negative binomial regression for count outcomes such as days at home, and non-transformed linear regression for normally distributed continuous outcomes (e.g., days at home), as appropriate. Given the multiple comparisons, we will use the Benjamini-Hochberg method for multiple comparisons for the secondary outcomes, with 0.2 as a prespecified false discovery rate.

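### The 1% Type 1 error behind the secondary power figures does not describe Benjamini-Hochberg at a false discovery rate of 0.2 on four outcomes, whose thresholds run from 5% to 20%

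*Protocol*

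**What the plan says.** Section 6.1 of the Protocol names the multiplicity rule for the secondary outcomes: "Benjamini-Hochberg method for multiple comparisons for the secondary outcomes, with 0.2 as a prespecified false discovery rate".

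Section 5.5.2 lists four secondary endpoints:
- "Total cost, discharge to 30-days post discharge"
- "Unplanned readmission within 30-days of discharge"
- "Days at home (the number of days spent at home from the day of discharge to 30-days later"
- "Percent of day lying down"

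The power analysis gives a power statement for each of these four. It sets their error rate at 1%, described as "with Type 1 error of 1%, approximately the type 1 error when using the Benjamini-Hochberg method as noted above". No other false discovery rate, and no other family size, appears in the Protocol.

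**The concern.** The power text ties its 1% to the rule in section 6.1, so the two should agree. They do not. Benjamini-Hochberg has no single per-test level. Its strictest step is the false discovery rate divided by the number of tests, and at 0.2 with four tests that step is well above 1%.

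Two things are at stake. The plan misdescribes how strict its secondary testing is, by a factor of at least five. The secondary power figures also refer to a test that will not be run. Secondary Aim 1 is worded as demonstrating benefit on days at home, activity and readmission, so the rule for calling those results positive should be unambiguous before the data are analysed.

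**Working it through.** **Inputs.** False discovery rate q = 0.2 (section 6.1). Number of outcomes m = 4 (section 5.5.2). Stated Type 1 error 1%, with 66 per arm (power analysis). 30-day cost: ratio of means 0.35, gamma dispersion 2.8. Readmission: control rate 23%, odds ratio 0.25. Sidedness is not stated for the secondary outcomes. I took two-sided, as for the primary, and ignored the site terms.

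**Trying to reproduce the 1%.** The rule compares the i-th smallest p-value with i × q/m:
- 1 × 0.2/4 = 0.05
- 2 × 0.2/4 = 0.10
- 3 × 0.2/4 = 0.15
- 4 × 0.2/4 = 0.20

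The strictest step is 5%. Other routes to 1%:
- Halving for one-sided testing gives 0.05/2 = 2.5%.
- A first step of exactly 1% needs 0.2/0.01 = 20 outcomes, or q = 4 × 0.01 = 0.04 with four.
- A rate of q = 0.05 gives 0.05/4 = 1.25%, which is roughly 1%.

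None of these is what section 6.1 states.

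**Why p ≤ 0.05 always passes.** A p-value of rank i passes if it is at or below i × 0.05. Since i is at least 1, any p-value at or below 0.05 meets its own threshold. If all four are at or below 0.20, all four are declared positive.

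**Error per outcome.** Simulated with independent two-sided tests:

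| Real effects among the other outcomes | False positive rate for a null outcome, q = 0.2 |
|---|---|
| 0 (no effect anywhere) | 6.7% to 6.8% |
| 1 | about 11.5% |
| 2 | about 16% |
| 3 | about 20% |

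**Power for 30-day cost.** The standard error of the log ratio is √(2 × 2.8/66) = 0.2913, and |ln 0.35| = 1.0498, so z = 1.0498/0.2913 = 3.604.
- At 1%: Φ(3.604 − 2.576) = 84.8%
- At 1.25%: Φ(3.604 − 2.498) = 86.6%
- At 5%: Φ(3.604 − 1.960) = 95.0%

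The stated figure is 80%.

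**Power for readmission.** The control odds are 0.23/0.77 = 0.2987. Multiplying by 0.25 gives 0.0747, a rate of 6.95% on intervention.

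*Wald test on the log odds ratio.* The standard error is √[1/(66 × 0.23 × 0.77) + 1/(66 × 0.0695 × 0.9305)] = 0.5656, and z = 1.3863/0.5656 = 2.451.
- At 1%: Φ(2.451 − 2.576) = 45.0%
- At 1.25%: Φ(2.451 − 2.498) = 48.1%
- At 5%: Φ(2.451 − 1.960) = 68.8%

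*Pooled comparison of proportions.* The difference is 0.1605, the null standard error 0.0621 and the alternative standard error 0.0605.
- At 1%: Φ[(0.1605 − 2.576 × 0.0621)/0.0605] = 50.3%
- At 1.25%: 53.5%
- At 5%: 73.9%

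The stated 80% is approached only at a two-sided level of about 10% (79.0% Wald, 83.2% pooled), which is the same as one-sided 5%.

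**The other two outcomes.** The lying-down calculation needs a control mean that the Protocol does not give. Assuming 5 to 24 hours, power at 1% is 97% or more, so the claim of over 90% survives. For days at home the power text names a log-normal model but a negative binomial dispersion. It does not define a single calculation, and I draw nothing from it here.

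**The case against.** The strongest reply is that the 1% is only a planning assumption. It appears once, in the secondary power paragraph. The operative rule is in section 6.1, where the rate of 0.2 is declared openly and in advance. The sample size comes from the primary outcome at a two-sided 5%. Planning at 1% when the rule tests at 5% or more understates power, as 30-day cost shows (84.8% against 95.0%). All of this stands, and it limits the seriousness of the point.

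A reader might infer more in three ways that the document does not support:
- *That the trial hides a 20% chance of a false secondary claim behind a 1% label.* The 20% chance of at least one false positive when nothing is real is the declared rate itself, not a product of the mismatch. Four unadjusted tests at 5% would give 1 − 0.95⁴ = 18.5%.
- *That 0.2 is the slip and 0.05 was meant.* A rate of 0.05 fits the 1% text better, but nothing in the Protocol says which figure is wrong. A rate of 0.2 for secondary outcomes is a permissible choice if its consequences are stated. Even at 0.05 the steps run from 1.25% to 5%, so 1% would be a loose label.
- *That the 1% makes every secondary power figure too pessimistic.* Readmission falls short of its stated 80% at both 1% and 5%.

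The reply does not rescue the statement itself. The power text says its 1% approximates the rule in section 6.1, and it does not.

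**Conclusion.** The point holds as the correction of a wrong stated figure. With q = 0.2 and four outcomes, the strictest threshold is five times the stated 1% and the most lenient is twenty times. The 5% to 20% range follows from the Protocol's own numbers without further assumption. The per-outcome error rates rest on independence. 30-day cost, readmission and days at home cover the same 30 days and are probably correlated, which would change those rates but not the thresholds.

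The recomputed power rests on two-sided tests, 66 per arm, no site terms and the Protocol's own effect sizes. On that basis, changing the error rate alone does not put the paragraph right: 30-day cost comes out above its stated power, and readmission below it at both levels.

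The primary test, the sample size and the conduct of the trial are untouched. This is a should-fix.

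**What to change.** Reconcile section 6.1 and the power analysis before the analysis begins, since a choice made after seeing the p-values would be data-driven. Either route is acceptable.

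1. **Keep 0.2.** Delete the 1%, state that the four thresholds are 5%, 10%, 15% and 20%, and recompute and restate the secondary power at 5%, the strictest step. The cost is a few sentences, and an open statement that secondary claims are held to a lenient standard.
2. **Keep about 1%.** Change the false discovery rate to match (0.05 gives a first step of 1.25%) and restate power at that level. The cost is fewer secondary results called positive, and readmission power of only about 48-54% for the odds ratio of 0.25.

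Under either route, state the sidedness and correct the readmission power. The stated 80% is not reached at 66 per arm under two-sided testing at 1% or 5%.
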